Many studies have been conducted for the improvement of quality of life and symptom management in patient with cancer lately. However, study for cough after lung cancer surgery is rarely conducted relative to its frequency.

The aim of the present study is to evaluate the efficacy and safety of MMDT for cough after lung cancer surgery. For this, a randomized, double-blind, placebo-controlled, multicenter trial will be conducted.

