### Sample size

2.4

Sample size calculation was conducted based on previous study that reported efficacy of MMDT on prolonged cough after lung cancer surgery.^[7]^ There was no study evaluated efficacy of MMDT using Leicester Cough Questionnaire (LCQ) in patients with lung cancer, thus, the changes of Short-From 36 (SF-36) score of the previous study were transformed to LCQ score. The mean differences of LCQ scores were hypothesized to be 8.40 and 5.52 in MMDT group and placebo group, respectively, and the standard deviation was hypothesized to be 3.45. The following formula was used to calculate the sample size. The calculation was performed using 95% power, and a 5% significance level 
[figure not shown]

Considering a drop-out rate of 20%, the needed sample size is approximately 48 participants for each group. Therefore, a total of 96 participants are needed for the present study.

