#### Safety assessment

2.12.2

All the safety related variables such as vital signs and laboratory test results will be compared between MMDT group and placebo group at every visit. We will check whether there is a significant difference between the 2 groups by *t*-test and whether there is a change beyond the normal range. The incidence of AEs will be compared by chi-square test. The statistical analyses for safety will be conducted by ITT analyses.

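### Safety is a stated aim, but section 2.12.2 compares the arms only by significance tests, which at 48 per arm cannot support a favourable safety statement

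*Protocol article*

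**What the plan says.** The Introduction gives the aim as "The aim of the present study is to evaluate the efficacy and safety of MMDT for cough after lung cancer surgery". Section 2.4 derives the sample size from LCQ change alone and concludes: "Therefore, a total of 96 participants are needed for the present study". No AE rate and no safety margin enter that calculation.

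Section 2.12.2 sets out the safety analysis. At each visit the arms are compared on vital signs and laboratory results: "We will check whether there is a significant difference between the 2 groups by *t*-test and whether there is a change beyond the normal range". AEs get one sentence: "The incidence of AEs will be compared by chi-square test". The analysis set is the ITT set, which section 2.12.1 defines as randomised participants who took at least one dose. The .05 threshold is stated in section 2.12.1 and not repeated for safety. Section 2.12.2 names no between-arm estimate or confidence interval.

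**The concern.** A test for a difference suits the question of whether an effect has been shown. A favourable safety statement needs the opposite: some bound on how much harm the data still allow. A non-significant test gives no such bound, least of all in a trial that was never sized on harms. The normal-range check in 2.12.2 is a second safety criterion, but it has no between-arm rule and does not limit an excess in the MMDT arm.

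At stake is the wording of the safety conclusion. If the report follows 2.12.2 and gives only test results, a finding of no significant difference in AEs could be taken as reassurance in recently operated lung cancer patients, although the data may be compatible with a large excess.

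**Working it through.** **1. Reproduce the plan's sample size (section 2.4).** Inputs: "The mean differences of LCQ scores were hypothesized to be 8.40 and 5.52 in MMDT group and placebo group, respectively"; "the standard deviation was hypothesized to be 3.45"; "The calculation was performed using 95% power, and a 5% significance level". The number of sides is not stated.

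- Difference: 8.40 - 5.52 = 2.88.
- n per arm = 2 × [SD × (z0.975 + z0.95) / difference]² = 2 × [3.45 × (1.960 + 1.645) / 2.88]² = 37.3, so 38.
- With 20% drop-out: 38 / 0.80 = 47.5, so 48 per arm and 96 in total.

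This matches the article. A one-sided calculation gives 32, then 40 per arm, and does not match. The size is therefore a two-sided .05 calculation on LCQ alone.

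**2. Denominator for safety.** The safety set is all dosed randomised participants. Someone who drops out after a dose still counts for AE incidence, so up to 48 per arm is the right figure.

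**3. Chance that the chi-square test misses a true AE excess.** The article gives no AE rates, so all rates here are assumptions, shown over a range. For each pair of counts (x in placebo, y in MMDT, n = 48), the uncorrected Pearson statistic is ((x - y)/n)² / [p(1 - p) × 2/n], with p = (x + y)/(2n). The result is significant if the statistic exceeds 3.841. Summing the binomial probabilities of all non-significant pairs gives the miss probability.

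| Placebo v MMDT | Type of excess | Missed |
|---|---|---|
| 5% v 15% | 10 points | 0.59 |
| 10% v 20% | 10 points and doubling | 0.71 |
| 20% v 30% | 10 points | 0.80 |
| 5% v 10% | doubling | 0.83 |
| 20% v 40% | doubling | 0.41 |
| 25% v 50% | doubling | 0.28 |
| 30% v 60% | doubling | 0.15 |

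The result for 10% v 20% does not depend on a favourable choice of test: the normal approximation gives 0.72, and Yates' correction or Fisher's exact test gives 0.82. For 80% power at those rates, 199 per arm would be needed.

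**4. The t-test on a vital sign or laboratory value.** For one variable at one visit with 48 per arm, a true shift of 0.5 SD gives a noncentrality of 0.5 × √(48/2) = 2.45 on 94 degrees of freedom. The miss probability is 0.32. Power of 80% needs a shift of about 0.58 SD.

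**5. What a non-significant AE result leaves open (Newcombe 95% interval from Wilson limits).**

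- 5/48 in each arm: the observed risk is 10.4%, with Wilson limits 4.5% and 22.2%. The difference is 0, and the upper limit is √[(0.222 - 0.104)² + (0.104 - 0.045)²] = 0.131. By symmetry the interval is about -13 to +13 points. A doubling from 10.4% would be an excess of 10.4 points, which lies inside it.
- 12/48 (MMDT) v 5/48 (placebo): the difference is 25.0% - 10.4% = 14.6 points. The chi-square statistic is 3.50, P = .06, so not significant. The interval is -0.9 to +29.6 points.

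**The case against.** The strongest reply is that nothing here is misstated. Section 2.12.2 says what will be compared and by which test, and naming a test does not rule out reporting incidences and intervals as well. This is a condensed article; the full protocol (version 1.1) and any analysis plan are not shown, and such reporting detail may stand there. The efficacy section names no interval either, which points to brevity.

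Much of this stands. A reader might infer that the plan treats P>=.05 as proof of safety; the article says no such thing. A reader might also infer that a null result is the likely outcome under any material harm. That is not so: a 0.5-SD shift is missed with probability 0.32, an AE excess of 25% v 10% with 0.49 and 30% v 10% with 0.29, each less than half. These are also single-test figures, while vital signs and laboratory values are tested at every visit. Nor is significance the only safety criterion, given the normal-range check. The AE figures rest on assumed rates, and for a doubling the miss probability varies widely with the base rate.

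The reply does not remove the point. Section 2.12.2 does more than leave the comparison open: it frames the between-arm safety question as whether a significant difference exists. That can be judged as written, and it poorly serves an aim that names safety.

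**Conclusion.** The point holds as a weakness in the stated method, and a change is worth making. The only between-arm safety comparisons that 2.12.2 states are significance tests. At up to 48 per arm a non-significant AE test is weak evidence: over the assumed rates, a 10-point excess is more likely missed than found, while a doubling ranges from mostly missed at a low base rate to mostly detected at a high one. The interval around equal counts of 5/48 makes the same case without assuming true rates, though the counts are illustrative.

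The article contains no rule equating non-significance with safety, so this concerns what the planned tests can support and is not an error of interpretation already made. It rests on a two-sided .05 level, the uncorrected chi-square test and full dosing of all 96 participants.

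**What to change.** In section 2.12.2, at the sentence "The incidence of AEs will be compared by chi-square test", change the basis of the comparison from testing to estimation:

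- For AEs, report the risk in each arm and the risk difference (MMDT minus placebo) with a 95% confidence interval, for example Newcombe's.
- For vital signs and laboratory values, report the between-arm mean difference in change from baseline with a 95% confidence interval, and keep the normal-range check.
- State that safety will be described from these estimates and intervals, and that P>=.05 will not be taken as evidence of safety or of equal safety.

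No margin is needed for this, because the intervals serve description and not a formal safety claim. If the full protocol or analysis plan already says this, a sentence bringing 2.12.2 into line is enough. The cost is a few sentences and a little more output, with no extra patients, visits or data. The downside is a more guarded safety conclusion, because the intervals will be wide.

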### Safety outcomes

2.11

All variables related to the participants’ safety including vital signs, physical examination, hematologic test, biochemical test, and urine test will be documented on the CRFs at every visit. Any AEs that occur after taking investigational drug will be documented on the CRFs. If the AE is severe and related to the investigational product, the participant will be withdrawn from the study, and the appropriate treatment and reimbursement will be provided to them.

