#### Efficacy assessment

2.12.1

The baseline characteristics will be analyzed by a *t* test for continuous variables or a chi-square test (Fisher's exact test will be conducted when the expected value is < 5) for categorical variables. If the normality assumption is not satisfied for the continuous variables, Mann-Whitney *U* test will be used. The last observation carried forward (LOCF) method will be used for missing values. For the efficacy assessment, an independent *t*-test will be conducted to compare the mean differences between the baseline and visit 4 for the 2 groups. In addition, paired *t*-test will be conducted to see intergroup changes between baseline and visit 4. Statistical analyses for efficacy will be conducted for both the ITT (intention-to treat, all randomized participants who administered at least single dose of investigational product), and PP (per-protocol, participants who completed the study without any major protocol deviations). The ITT analyses will be the primary analyses and PP analysis will be for reference. If the *P* value is <.05, the result will be considered as statistically significant. There is no plan for interim analysis.

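### Section 2.12.2 leaves the plan's own small-count rule out of the AE test, and as written t-tests all safety variables between groups at every visit, including baseline and categorical findings

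*Protocol article*

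**What the plan says.** **AE incidence.** Section 2.12.2 (Safety assessment) names one test: "The incidence of AEs will be compared by chi-square test". It gives no alternative for small counts and does not mention a continuity correction. Section 2.12.1 (Efficacy assessment) does have a small-count rule, "Fisher's exact test will be conducted when the expected value is < 5", but attaches it to the categorical baseline characteristics.

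**Other safety variables.** Section 2.12.2 states: "All the safety related variables such as vital signs and laboratory test results will be compared between MMDT group and placebo group at every visit". The method follows: "We will check whether there is a significant difference between the 2 groups by *t*-test and whether there is a change beyond the normal range". Section 2.11 (Safety outcomes) describes the safety variables as "including vital signs, physical examination, hematologic test, biochemical test, and urine test", recorded at every visit. The t-test is the only between-group test named for them.

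**Timing.** Section 2.1 gives four visits over four weeks. Section 2.9 defines Visit 2 as baseline and Visit 4 as the end of treatment.

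**The concern.** Evaluating safety is part of the stated aim, so the safety tests should match the data they will meet.

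On AEs, the safeguard sits where it matters least. Baseline tables are descriptive, while AE tables are a place where low counts can readily occur. A sparse AE could be called significant under 2.12.2 when the rule in 2.12.1, applied to the same table, would say otherwise. Since no correction is specified, two analysts could also report the same table differently.

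On the other variables, testing at every visit takes in comparisons at or before baseline, which cannot show a drug effect. Comparing the groups visit by visit does not use each participant's baseline value, whereas 2.12.1 does use change from baseline for efficacy. A t-test also has no sensible meaning for an unordered physical examination finding, and suits graded urine results poorly. The text does not say that the resulting p-values are descriptive.

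**Working it through.** **Inputs.** From 2.4: mean changes 8.40 and 5.52, SD 3.45, 95% power, 5% significance level, 20% drop-out, 48 per group. From 2.12.1: Fisher if an expected value is below 5; significance at P < .05. From 2.5: 1:1 allocation. The documents give neither AE rates nor the number of safety variables, so both are assumed and shown as ranges.

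**1. The plan's own figure.** With two-sided alpha, n per arm = 2 × [3.45 × (1.960 + 1.645) / 2.88]² = 37.3, rounded up to 38. Then 38 / (1 − 0.20) = 47.5, rounded up to 48 per arm and 96 in total. The stated size reproduces, and 48 per arm is used below.

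**2. When the small-count rule would apply.** With m cases in total and equal arms, the expected number of cases per arm is m/2. This is below 5 when m < 10. As an overall rate, 5/48 = 10.4%, so AEs occurring in fewer than about 10.4% of participants would be expected to meet the trigger.

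**3. Where the verdict changes.** For a vs b cases at 48 per arm, uncorrected chi-square is X² = 96(a − b)² / [m(96 − m)]. For 4 vs 0 this is 96 × 16 / (4 × 92) = 4.17, p = 0.041. Two-sided Fisher is 2 × C(48,4)/C(96,4) = 2 × 194,580 / 3,321,960 = 0.117. Enumerating all tables with m < 10, the two tests disagree at .05 only for these splits (in either direction):

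| Cases | Chi-square, uncorrected | Chi-square, Yates | Fisher |
|---|---|---|---|
| 4 vs 0 | 0.041 | 0.125 | 0.117 |
| 5 vs 0 | 0.022 | 0.066 | 0.056 |
| 6 vs 1 | 0.0497 | 0.116 | 0.111 |
| 7 vs 1 | 0.027 | 0.065 | 0.059 |

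The Yates column shows that the unstated choice of correction alone also changes the verdict in all four.

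**4. Overall type I error.** Exact enumeration at 48 vs 48 with no true difference, nominal 5%, assumed AE rates:

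| AE rate | Chi-square, uncorrected | Fisher |
|---|---|---|
| 2% | 1.2% | 0.03% |
| 3% | 2.8% | 0.15% |
| 5% | 5.2% | 0.65% |
| 8% | 6.1% | 1.4% |
| 10% | 5.9% | 1.7% |
| 20% | 5.2% | 2.7% |

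Uncorrected chi-square stays close to nominal or below it. Fisher is clearly conservative throughout.

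**5. Repeated t-tests.** At 5% each, the expected number of chance flags is 0.05 × the number of tests: 1 in 20 tests, 2 in 40, 3 in 60, 6 in 120. With 20 to 30 variables (assumed), the two post-baseline visits give 40 to 60 tests, and all four visits give 80 to 120. If tests were independent, the chance of at least one flag would be 1 − 0.95^20 = 64% and 1 − 0.95^60 = 95%. Repeated laboratory values are correlated, so these probabilities are only indicative; the expected counts do not depend on independence.

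**6. Skewed values.** Section 2.12.1 has a fallback, "If the normality assumption is not satisfied for the continuous variables, Mann-Whitney *U* test will be used", which 2.12.2 does not repeat. In simulation of lognormal data at 48 per arm (sigma 0.5, 1.0, 1.5), the t-test's error at nominal 5% was 4.9%, 4.7% and 3.4%, so there was no inflation.

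**The case against.** The strongest reply is that little is at stake. Uncorrected chi-square has a true size nearer 5% than Fisher does at assumed AE rates from 3% to 20%, and Fisher would stop flagging 4 vs 0, a doubtful gain in a safety comparison. This stands. It limits the point to consistency in four borderline splits and is the reason for showing a confidence interval beside the test.

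Second, AE incidence may mean only the proportion of participants with any AE, which need not be sparse. The text does not settle this, and no AE rate is given. The small-count point applies to whatever AE table has fewer than 10 cases.

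Third, 2.12.2 itself gives only vital signs and laboratory results as examples; physical examination and urine tests come from 2.11. The authors may never have meant to t-test a categorical finding. That is plausible, but the wording covers all safety variables and names no other between-group test. The same sentence also plans a check against the normal range, which deserves credit and is close to what categorical results need, although no comparison of it by group is described.

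Fourth, a full protocol or SAP may hold the Fisher rule, categorical methods and multiplicity handling, and their absence from an article is not a fault. This is accepted. What remains concerns the tests that the article does name and when it applies them.

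Fifth, unadjusted safety screening is common and errs towards false alarms. That is a reason to label the p-values descriptive, not to adjust them.

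**Conclusion.** The point holds as a modest inconsistency in stated rules. The plan applies a small-count rule to baseline tables and names chi-square alone for AEs. At 48 per arm this changes the verdict in 4-0, 5-0, 6-1 and 7-1. The t-test rule is too broad: it covers visits at or before baseline, does not use the baseline value, and on its wording reaches categorical findings.

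A reader might infer more, and the documents do not support it:

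- **That significant safety results in general cannot be trusted.** Chi-square error peaks near 6.1% across the assumed rates.
- **That 8 vs 2 is a further conflict.** It has 10 cases and an expected count of exactly 5, so the rule in 2.12.1 would not call for Fisher.
- **That skewed laboratory values invalidate the t-tests.** The simulation shows no inflation.
- **That the safety population is wrong.** The ITT set in 2.12.1 already requires at least one dose, and nothing here argues for regrouping by product taken.

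The table results rest on 48 analysed per arm. The error rates rest on assumed AE rates, and the count of chance flags on an assumed number of tests.

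**What to change.** Revise 2.12.2 as follows:

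- **AEs.** Apply the rule from 2.12.1 (Fisher's exact test when an expected count is below 5) and say whether chi-square is corrected otherwise. Report the risk difference with a score or exact 95% CI beside each comparison.
- **Continuous measures.** Limit mean comparisons to visits after baseline, as change from baseline or baseline-adjusted differences with CIs.
- **Categorical findings.** Summarise physical examination and categorical urine results, and the existing normal-range check, as counts or shift tables by group.
- **Interpretation.** State that safety p-values are descriptive.

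The cost is a few sentences and no new data. The downside is Fisher's conservatism (size about 0.03% to 2.7% at AE rates of 2% to 20%): it will rarely flag a sparse AE, so the confidence interval should carry the interpretation.

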### Data and safety monitoring

2.13

Pharm data, the contract research organization (CRO), will monitor this trial. Each institution participating in the present study will be monitored while this study is in progress. Auditing is not scheduled for this study. Double data entry and range checks will be conducted for improvement of data quality. AEs will be reported to IRBs, and suspected unexpected serious adverse reaction will be reported to MFDS.

### Ethics and dissemination

2.14

The present study has been approved by the Institutional Review Boards (IRBs) of all 5 institutions: the Korea University Guro Hospital(KUGH17284-001), Korea University Anam Hospital(ED17065), Korea University Ansan Hospital (AS17184-002), Gangnam Severance Hospital (3-2018-0058), and Inje University Ilsan Paik Hospital (ISPAIK 2017-11-026-001). The current protocol version is 1.1. Any information acquired from study participants will be dealt with confidentially. During the entire study, data will be handled by the participant identification code which is assigned to each participant at enrolment. All records from the study will be stored securely in locked cabinets or in password-protected electronic documents. Only investigators in charge will have the right to access the data. The results of the present study will be published in a scientific journal or presented through a scientific conference. There is no plan to public release the full protocol and personal datasets.

## Discussion

3

Cough is a symptom of many respiratory diseases such as tonsillitis, laryngitis, pharyngitis, lung cancer, asthma, bronchitis, pneumonia, and tuberculosis. A systematic review reported that several herbal medicines have positive effect on cough in patient with childhood cough variant asthma.^[19]^ However, that study only evaluated the efficacy of combination treatment of herbal medicines and conventional therapies, and excluded the patients with serious respiratory disease including chronic obstructive pulmonary disease and lung cancer. There are several clinical trials to investigate efficacy of herbal medicine for cough in patient with cough variant asthma, postinfectious cough, and allergic asthma.^[9,20,21]^ Although previous study showed that MMDT can improve chronic cough after lung cancer surgery, that study had a limitations of small and single-centre trial.^[7]^ A study protocol for the treatment of chronic dry cough using MMDT has already been published^[22]^; however, the present study has several distinctive features of relatively large scale, multicenter trial for patients with lung cancer. The present study is the first multicenter, randomized, controlled trial for evaluating the efficacy of MMDT in Korea. The results of this study might provide a new treatment for postoperative cough in patient with lung cancer surgery. We expect that the present study protocol will serve as a reference for planning further clinical trials to treat cough using herbal medicines.
